##### Missing data

Missing pre-post values will not be replaced by specific values, but be excluded from statistical analysis.

### Sample size calculation

#### Single-case data

The sample size needed for the abovementioned statistical analyses is different for the SCED and single-armed prospective study design. For the SCED design, the minimum sample size is *n* = 1. Instead, the power of the analysis depends on the number of observations [40, 41]. For randomization tests the lowest attainable *p*-value is calculated by dividing 1 by the number of possible permutations. In this study, the baseline phase, after removing the first four values because of a learning effect, can contain 5 to 24 measurement points, allowing 20 possible permutations. This corresponds with a lowest attainable *p*-value of 0.05 [56]. Of note, successful replication of the single-case experiment in additional participants with similar symptoms will improve the generalizability of the results [40, 41].

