### Study design and procedures

#### Study design

This study will apply a randomized replicated sequential ABC single-case experimental design (SCED), with a baseline (A), intervention (B) and follow-up (C) phase [36, 40]. SCED study designs demonstrate strong internal validity to determine the likelihood of a causal relationship between the intervention and outcomes. One entity is observed repeatedly over a certain time period under different levels of at least one independent variable. The power in SCEDs is related to the number of data points for each participant and not the number of participants. Each participant serves as his/her own comparison, thus controlling for confounding variables that can impact outcome and allowing heterogeneous clinical presentations. The internal validity of the SCED results can be improved by randomization techniques such as randomization of the starting time of the intervention. The downside is that the generalizability of the study results to the total population still depends on the number of participants included (i.e. replication of the findings) [40, 41]. The SCED lend itself perfectly to reflect on the reasons for the (likely) variability in the onset of NMES-induced effects on cognitive performance, looking at individual participant’s intervention courses. Thus, allowing to reflect on the existence of different potentially moderating characteristics. Several potential moderators have been suggested previously [4] and will be measured within this study. These include concomitant traumatic brain injury, psychological alterations, chronic pain, hemodynamic dysregulation, level of injury, respiratory failure, substance (ab)use, educational level, cardiovascular diseases, and intensive care admission [4]. In addition, a SCED design allows us to interpret after how many weeks the NMES leads to changes in performance on the momentary digital symbol substitution task. The aforementioned advantages of SCED studies indicate how this design offers additional information that is well fitted for an explorative study in a new topic.

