In the context of SCED studies, randomization does not refer to individuals being randomly allocated to treatment groups, but to the random onset of the intervention phase which is usually set within a fixed window of time in order to make this randomization more feasible [38]. In this study, a window of 9 to 24 measurement points (i.e. 3 to 8 weeks at the set frequency of three test assessments per week) will be employed in which the change of phase from baseline to intervention phase will be randomly determined. This determination will be done with a random number generator in Excel set to give a random number between 9 and 24. There will be a baseline phase ranging from 3 to 8 weeks, followed by an intervention phase of 12 weeks and a final follow-up phase of 3 weeks after a 12 week rest period with no measurements and no interventions. As we will exclude the first 4 measurements in the baseline phase from analysis, see Sect. "Statistical analysis", this leaves us at least 5 measurement points in this phase, 36 measurement points in the intervention phase and 9 measurement points in the follow-up phase. Neither participants nor researchers will be blinded to the phase of the intervention. Replication of the experiment will be done in 15 participants.

Finally, additional measurements will be done in a repeated manner according to a single-armed prospective design before baseline phase, at the end of the baseline phase, at the end of the intervention phase and at the start of the follow-up phase.

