##### Randomization test

Subsequently, randomization tests will be performed to test the null hypothesis that NMES does not have an effect on participant’s cognitive function. The observations of the baseline phase will be compared to those of the intervention and follow-up phases respectively. The test statistic “means of phase A minus means of phase B” will be chosen as the primary outcome of this study. In case visual analysis suggests delayed effects, the randomization test will be repeated with lagged data until the lowest p-value has been reached (one effect lag equals one day). The first 4 measurements in the baseline phase will be removed before calculating the means, since we expect a learning effect on the first trials, leaving between 5 and 20 measurement points depending on the randomly decided length of the baseline period. Studies that tested the statistical properties of a randomization test used in this type of design showed that the Type I error probability of the randomization test was maintained at an acceptable level [61].

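### The start window has 16 positions, not 20, so one participant's randomisation test cannot give a p-value below 0.0625, against the stated 0.05

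*Protocol article*

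**What the plan says.** The Study design section sets "a window of 9 to 24 measurement points (i.e. 3 to 8 weeks at the set frequency of three test assessments per week") for the change from baseline to intervention. The draw is made with a "random number generator in Excel set to give a random number between 9 and 24".

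The Randomization test section names the difference in phase means as the primary outcome. It says "The first 4 measurements in the baseline phase will be removed before calculating the means", "leaving between 5 and 20 measurement points depending on the randomly decided length of the baseline period".

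The Sample size calculation section (Single-case data) justifies this test by its attainable p-value. It states that "the lowest attainable *p*-value is calculated by dividing 1 by the number of possible permutations", that after the same removal the baseline "can contain 5 to 24 measurement points, allowing 20 possible permutations", and that "This corresponds with a lowest attainable *p*-value of 0.05".

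**The concern.** Two sections give different baseline ranges after the same four values are removed: 5 to 20 in one, 5 to 24 in the other. The wider range is the one used to count permutations. Removing early observations shifts both ends of the range equally and cannot create start positions, so the count of 20 looks like a lower limit taken after removal paired with an upper limit taken before it.

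The attainable p-value is the only quantitative justification that the article gives for the primary test. With 20 positions, a participant could just touch 0.05, and only if the observed start gave the single most extreme statistic. With 16 positions, even that result stays above 0.05. A participant with a clear effect would then be reported as not significant at that level because of the width of the draw, and this could be misread as evidence of no effect.

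**Working it through.** **Inputs**

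- Start window: 9 to 24 measurement points (Study design).
- Values removed from the baseline: 4 (Study design; Randomization test).
- Baseline range after removal: 5 to 20 (Randomization test) or 5 to 24 (Sample size calculation).
- Intervention phase 36 points, follow-up 9 points (Study design); total per participant 54 to 69 (Statistical analysis, Single-case data).

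**Formulas**

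Number of positions k = upper limit − lower limit + 1. Lowest attainable p = 1/k, the article's own rule.

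**Reproducing the stated figure**

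From 5 to 24: k = 24 − 5 + 1 = 20, and 1/20 = 0.05. The stated figure follows from the stated range, so the division is right and the range is the problem.

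**Applying the rule to the design as described**

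| Range | Source | k | Lowest p |
|---|---|---|---|
| 9 to 24 | Study design | 24 − 9 + 1 = 16 | 0.0625 |
| 5 to 20 | Randomization test | 20 − 5 + 1 = 16 | 0.0625 |
| 5 to 24 | Sample size calculation | 24 − 5 + 1 = 20 | 0.05 |

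The two ranges of 16 are the same window before and after removal: 9 − 4 = 5 and 24 − 4 = 20.

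**Cross-check on the totals**

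9 + 36 + 9 = 54 and 24 + 36 + 9 = 69, which matches the stated totals. Both ends of the window, 9 and 24, are therefore included. Twenty positions from 9 upwards would need a window of 9 to 28, about 9.3 weeks. That exceeds the stated 8 weeks and would make the largest total 28 + 36 + 9 = 73.

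**Check by enumeration**

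A near-perfect step effect was generated for every possible start, the first four points were dropped, and the statistic was computed at all admissible starts. The smallest p-value was 0.0625, both one-sided and two-sided, for the 9 to 24 window. It was 0.05 for a 9 to 28 window.

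**Do other planned steps lower the floor?**

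No. Lagging changes which observations count towards each phase mean, and the randomised marker method changes where missing values sit. Neither adds admissible assignments, so the observed one remains at best 1 of 16.

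The Missing data section describes the relevant window as 4 to 8 weeks. Read literally, that is 12 to 24 points: k = 13 and 1/13 = 0.077, further from 0.05.

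**The case against.** The count itself cannot be rebutted: the draw, the range after removal and the totals all agree on 16. The objections concern how far the consequence reaches.

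- **No significance level is stated for this test.** This stands. That 0.05 is the benchmark is an inference from its being offered as the lowest attainable p-value. If another level is meant, the stated 20 and 0.05 are still wrong.
- **The study is exploratory and also uses visual analysis and non-overlap measures.** This stands as context. The article nevertheless plans a formal null-hypothesis test and names its statistic the primary outcome.
- **The full protocol or analysis plan may contain a combined test.** A reader might infer that the trial as a whole cannot reach 0.05. The article does not support that. The floor applies to each participant's own test, and a test combined over independently drawn starts could go well below it: two participants both at the floor already give (1/16)² = 0.0039. It can be said only that the article describes no such test.
- **A reader might infer a large false-positive problem from the miscount.** If 0.0625 were accepted in each of 15 participants with no true effect, the chance of at least one positive would be 1 − (15/16)^15 = 62%. With the stated 20 positions and 0.05 it would already be 1 − 0.95^15 = 54%. Most of that figure is multiplicity, and the article does not say that one positive participant would count as a trial-level result.
- **A reader might take the general remark in Study design, "The power in SCEDs is related to the number of data points for each participant and not the number of participants", as a second error.** It is a broad statement about single-case designs. The sample size section itself ties the p-value floor to permutations, so the article does not confuse the two.

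**Conclusion.** The sample size section is wrong as written. The design has 16 start positions, not 20, and the lowest attainable p-value for one participant is 0.0625, not 0.05. No individual randomisation test can reach 0.05, whatever the size of the effect.

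The count of 16 rests on the draw being inclusive at both ends, which the minimum of five baseline points and the totals of 54 to 69 confirm. The statement about 0.05 rests on reading that value as the intended level. No assumption about effect size, autocorrelation or learning is needed.

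The error bears on the justification of the primary test and should be corrected before results are interpreted. It does not show that the replicated experiment as a whole is without power.

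**What to change.** **Text correction.** In the Sample size calculation section, give 5 to 20 measurement points, 16 possible permutations and a lowest attainable p-value of 0.0625. State that a single participant's test cannot reach 0.05, and how individual p-values will be read, for example descriptively alongside the visual analysis and non-overlap measures. This costs a few sentences and no data collection.

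**If inference at 0.05 is wanted, there are two options.**

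1. Prespecify a randomisation test combined across the replicated participants, for example one based on the sum of their p-values. The critical value should be computed for the number of participants and start positions actually analysed. A cut-off fixed in advance for 15 participants would no longer hold after any dropout, and the article allows for dropouts. This costs one additional analysis and no extra measurements.
2. Widen the draw to at least 20 positions, such as 9 to 28, for participants not yet randomised. This adds up to four baseline sessions, about 1.3 weeks, to the longest baseline. It would also mean amending the 3 to 8 week baseline and the figures that depend on it in the Abstract, Study design, Study procedures, Single-case data, Randomization test, Missing data and Sample size calculation sections. As a change to the approved design, it would probably also have to be notified to the ethics committee and updated in the registry, as the Methods section requires for important modifications. The cost is therefore clearly higher than that of the first option.

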#### Secondary data

For the single-armed prospective study design we have estimated the sample size needed in order to have sufficient power (Power = 0.80) for evaluating a Time effect (over 4 time points) of cognitive test performance changes with repeated measures ANOVA. We found no previous studies examining the effect of any muscle activity intervention in spinal cord injury subjects. Therefore, the required effect size was estimated to be similar to that from a meta-analysis examining the effect of resistance exercise interventions on general cognitive function in healthy adults [66]. The overall effect size (Cohen’s d) was 0.71 (0.30–1.12) for resistance exercise. The correlation among repeated measures for this cognitive test battery that was found to be ≥ 0.77 in a previous SCI study [43]. G*Power 3.1.9.7 estimated that the minimum total sample size should be 7. Taking into account potential drop-outs and the uncertainty of the effect, we decided to aim for a total sample of 15 included participants.

### Data management

All the participant data will be coded and pseudomized to protect their privacy. The repeated cognitive test will be administered using a secured smartphone application (see www.m-path.io/landing), which was designed for use in clinical settings and research and is General Data Protection Regulation (GDPR) compliant. Participants will register to m-Path with their study code instead of their personal name. With a password, one of the researchers can access a dashboard where data from all included participants will be visible. Other test results including participant identification details will be stored at Adelante Hoensbroek in a locked cabinet with restricted access. The key will be kept in another locked cabinet. The test results with participant identification will only be accessed again after coding and de-identifying the data in order to hand them over to participants requesting their test results. The data will be stored for 15 years. Blood samples will be destroyed after analysis, which is expected to take place within one year after blood collection. We intend to make pseudomized data from our study available according to the FAIR principle, such that it is Findable, Accessible, Interoperable and Reusable. Both negative and positive results will be made public. Our results will be presented on the Dutch national rehabilitation medicine congress and international rehabilitation/neuroscience congresses so that rehabilitation professionals are more aware of the benefit of muscle training or maintaining a healthy body overall on the brain and cognitive function, and so that neuroscientists will understand the relevance of neuromuscular electrical stimulation as one of the muscle training strategies to investigate the exercise-cognition link. The results will be conveyed locally to spinal cord injury subjects in our rehabilitation center in Hoensbroek and in the Maastricht University Medical Center (MUMC +). We will inform other national spinal cord injury clinics of the results and we will discuss the findings in the national work group of the Dutch rehabilitation society for movement and sport. Finally, the results will be submitted to a peer-reviewed journal.

#### Risks and harms

The use of electrical stimulation is generally safe. It has even been used unsupervised in spinal cord injury subjects during sleep [67]. However some adverse events or inconveniences that have been reported previously in literature are a red, raised or itchy skin; muscle pain; increased neuropathic pain; uncomfortable feeling; orthostatic hypotension (dizziness, light-headedness, blurred vision, palpitation or shortness of breath); in some cases pain from a spasm may occur. The adverse events reported are temporary added risks that disappear once the stimulus/stimulation has stopped [68]. In case the subject feels uncomfortable during electrical stimulation, they will be informed that the stimulation can be interrupted. Participants with a lesion level above T6 may experience autonomic dysreflexia in response to the electrical stimulation. Whenever this occurs, stopping the electrical stimulation should solve the problem. Participants with lesion levels above T6 will be explained how they can recognize signs of autonomic dysreflexia. Whenever autonomic dysreflexia has occurred during the NMES training period participants are asked to contact the medical professional who’s telephone number is provided to them at the beginning of the project and in the participant information. The sponsor has a liability insurance which covers for damage to research participants. All adverse events reported spontaneously by a participant or observed by the investigator will be recorded.

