#### Study procedures

The experimental design is illustrated in Fig. 1. Upon the first appointment (T1), participants will sign an informed consent and undergo baseline examinations consisting of questionnaires and clinical tests. A smartphone application for repeated monitoring of cognitive function will be installed on their smartphones and they will be familiarized with the cognitive tests and neuromuscular electrical stimulation intervention. On a separate day (T2), within seven days from the first appointment, they will undergo a series of cognitive tests and venous blood samples will be collected. Furthermore, they will fill in a second list of questionnaires and undergo a clinical evaluation of strength and spasticity. This will be followed by a no-treatment baseline period with a random length of 3–8 weeks. Upon the third (T3), fourth (T4) and fifth (T5) visit, the oral cognitive tests, venous blood sample collection and questionnaires from T2 will be repeated. During the third visit (T3) the participants will receive their own NMES device for home-based training and they will be asked to return it 12 weeks later on the fourth visit (T4). All participants will undergo the same intervention. During the fourth visit (T4) the clinical evaluation of strength and spasticity that was done at T2 will be repeated. Between T2 and T4 and between T5 and T6 participants will undergo smartphone cognitive tests 3 times per week. At the end of the study, no additional tests will be done. Participants will be requested to write in a diary the specifications of the NMES session (duration, intensity) after each session and indicate when they performed a cognitive test. They can also write down any problems they encountered using the NMES device or smartphone application. Participants receive a telephone call once a week by one of the researchers to assess how they feel, be reminded of the diary and to assure there are no technical issues with the NMES device or smartphone application. Participants are allowed to withdraw from the study at any time. Available data from these participants will be included in the data analyses whenever possible.

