### Intervention

The intervention consists of 12 weeks NMES which will be done using the Pierensymphony M, serie A, article number 104800 (10,003,566) (manufactured by Pierenkemper GmbH and distributed by schwa-medico Nederland B.V.), a two-channel NMES device designed, and CE marked for muscular electrical stimulation (CE 0482). After a familiarization session, the intervention will be home-based, three times a week, with at least 1 day between stimulation sessions and 2 days between a stimulation session and testing day. Electrical stimulation will be done on the quadriceps muscles of both legs simultaneously. For each leg, one electrode is placed on the proximal lateral side and one on the distal medial side of the quadriceps muscle (see Fig. 2). Electrical stimulation will take 30 min, at a stimulation frequency of 50 Hz, and a pulse width of 400 μs. We will choose the highest intensity that is easily supported by the participant without inducing discomfort with a maximum intensity of 100 mA. We should at least see a visible or palpable contraction or the participant will be excluded. The activation within the activation-rest cycle consists of a 1 s ramp-up, 7 s full activation and 1 s ramp-down, followed by 18 s rest. Every 4 weeks the rest period will be diminished with 3 s until the rest phase is equal to the activation phase (9 s). Participants may continue their normal treatments, which may consist of physiotherapy. However, they will be asked not to change their physical activity habits during the experiment.

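### Adverse event recording rests on spontaneous reports and investigator observation although stimulation is home-based, and the weekly call and diary are not tied to it

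*Protocol article*

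**What the plan says.** The recording rule is the last sentence of Risks and harms in the protocol article: "All adverse events reported spontaneously by a participant or observed by the investigator will be recorded".

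The same section lists the events expected from the literature: "However some adverse events or inconveniences that have been reported previously in literature are a red, raised or itchy skin", followed by muscle pain, worse neuropathic pain, discomfort, orthostatic symptoms and painful spasm. It describes these as temporary and ending with the stimulation. It treats autonomic dysreflexia separately, for lesions above T6: "Whenever autonomic dysreflexia has occurred during the NMES training period participants are asked to contact the medical professional".

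On the setting, the Intervention section states: "After a familiarization session, the intervention will be home-based, three times a week".

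Study procedures describes two routine channels between visits:
- **The call.** "Participants receive a telephone call once a week by one of the researchers to assess how they feel". The call also serves as a diary reminder and a check for technical faults.
- **The diary.** Participants enter duration and intensity after each session. In addition: "They can also write down any problems they encountered using the NMES device or smartphone application".

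Neither channel is mentioned in the recording rule, and neither is described as a source of adverse event data. The Demographic and clinical assessments section adds a pain questionnaire at T2 to T5.

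**The concern.** The rule has two routes, and both are weak in this setting. Observation needs an investigator present, and during the 12 weeks of stimulation there is rarely one. Spontaneous reporting needs the participant to notice an event, judge it worth mentioning and mention it unprompted. The Participants section admits AIS grades A, B and C, a scale that the article says covers sensation as well as strength. A skin reaction on the thigh may therefore go unfelt in some participants and come to light only if they are asked whether they have looked.

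At stake is how the harms data can be read. Under a passive rule, an absence of reported skin or orthostatic events could mean that none occurred or that none was mentioned. Reporting habits also differ between people, so differences between participants would partly reflect who volunteers information. In a single-case design, where results are read person by person, that unevenness matters as much as the total. The primary cognitive analysis is not affected.

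**Working it through.** The plan gives no adverse event figure to reproduce. The check is exposure arithmetic followed by a comparison of sections.

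**Inputs**
- Participants (Study design): "Replication of the experiment will be done in 15 participants".
- Duration (Intervention): "The intervention consists of 12 weeks NMES".
- Frequency and setting (Intervention): three sessions a week at home.
- Baseline length (Study design): 3 to 8 weeks.
- Contact (Study procedures): one call a week.

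**Exposure**
- Sessions per participant: 3 x 12 = 36.
- Sessions in total: 36 x 15 = 540.

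**Contact already planned**
- Intervention calls: 12 per participant, so 12 x 15 = 180, or one call per 3 sessions.
- Baseline calls: 3 to 8 per participant, so 3 x 15 = 45 to 8 x 15 = 120 in total. This assumes that the calls run from the start of baseline; the article does not restrict them to a phase.

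**What the investigator can observe.** The device is handed over at T3 and returned at T4, 12 weeks later, and Study procedures describes no visit in between. The listed events are said to end when stimulation ends. Few of them would still be visible at T4, so almost everything depends on what participants report.

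**Which channel prompts each listed event**
- *Autonomic dysreflexia:* participants with lesions above T6 are taught the signs, and participants are asked to contact a medical professional. This is actively requested.
- *Muscle, neuropathic and spasm pain:* the pain questionnaire is completed at T2, T3, T4 and T5. This is systematic, but only T4 falls at the end of stimulation, so it is not a session-level or weekly record.
- *Skin reaction:* no specific prompt is described. The general question on the call may elicit it if the participant has noticed it.
- *Orthostatic symptoms and discomfort:* no specific prompt is described, beyond the general question on the call.
- *Diary notes:* optional, and worded around use of the device and the app rather than bodily effects.

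**Result.** Two groups of events have a dedicated channel and the rest depend on a general prompt. No channel is tied to the recording rule. The size of any under-count cannot be calculated: it needs a true event rate and a capture rate for spontaneous reporting, and the documents give neither.

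**The case against.** The case on the other side is substantial, and several parts of it stand.

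- **The rule does not exclude other sources.** It says what will be recorded, not that anything else will be discarded. An event mentioned on the call or written in the diary could well be treated as reported. A reader might infer that events count solely if volunteered or seen; the text does not say so. What remains is that the rule does not name these sources.
- **Active elements exist.** The weekly question about how participants feel is a repeated open prompt, the diary invites problem reports, dysreflexia reporting is requested, and pain is measured at four visits. Ascertainment is not purely passive.
- **A definite under-count is not shown.** A reader might conclude that harms are certain to be under-counted. Without rates, incomplete capture is a likely consequence, not a demonstrated one.
- **Baseline is not left out.** A reader might infer that the stimulation-free baseline would have no adverse event count. Nothing limits the recording rule to the intervention phase; only the dysreflexia instruction is tied to the training period.
- **The small sample is a separate matter.** Zero events in 15 participants leaves a one-sided 95% upper limit of 1 - 0.05^(1/15) = 0.181. That 18% holds even with perfect ascertainment, so it is no evidence against the recording method.
- **Safety is not an endpoint.** The endpoints are cognition and BDNF, and the remark that stimulation is generally safe introduces literature, not a planned trial conclusion. This limits the weight of the point.
- **The article is condensed.** A call script or event form may sit in the full protocol. Their absence here would be no finding. The article does, however, print a collection rule, and that rule fits a home-based intervention poorly.

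**Conclusion.** The point holds as a cheap improvement to data collection. The printed rule relies on spontaneous report and observation for about 540 home sessions, in participants some of whom may not feel the first event on the list. The call and diary that could close the gap are not linked to it. Listed events other than autonomic dysreflexia and pain are likely to be captured incompletely and unevenly, to an extent the documents do not allow anyone to quantify.

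This rests on three assumptions: that no visits take place between T3 and T4 beyond those described, that the call has no adverse event script in the full protocol, and that impaired sensation at the electrode sites is present in at least some AIS A to C participants. If a script exists, the remaining change is one sentence linking it to the recording rule.

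**What to change.** Reconcile Study procedures with Risks and harms:

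1. State that each weekly call, in baseline and intervention weeks alike, asks a short fixed set of questions on the events already listed in Risks and harms, including whether any skin change was seen at the electrode sites (in baseline, the same area of the thigh).
2. State that events reported on the call or in the diary are recorded as adverse events, alongside spontaneous reports and observations.
3. Report solicited and spontaneous events separately, by phase. Because baseline lasts 3 to 8 weeks and the intervention 12, express them per participant-week.

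The same questions in both phases give a like-for-like count, so background complaints in this population are not attributed to stimulation. The change concerns data collection alone and leaves clinical management, the design and the primary analysis as they are. The cost is a few extra minutes in a call that already takes place, and more minor events to log.
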